#### Secondary Measures

##### Demographics

Patient demographics including age, gender, weight, height, blood pressure (if known), and race will be collected through a self-reported questionnaire.

##### Symptoms

Study staff will ask patients in both groups about their symptoms using the following question: “Have you experienced any of these conditions in the last two weeks?” and the following response choices: chest pain, fainting, shortness of breath, palpitations, and weakness.

##### Risk Factors

The patient’s medical history will be assessed using the following question: “Do any of the following apply to your medical history?” and the following response choices: diabetes, overweight or obese, high blood pressure, high cholesterol, family history of heart disease, and smoking.

##### Site-Specific Health

Depending on the UF Health specialty clinic that the patient is visiting, this section of the questionnaire will be slightly different. Conditions relevant to that site will be listed, and the patient will select the ones that apply to them. Then, they will be asked to state how long, in years, they have experienced those conditions.

##### Heart Health

The final section of the questionnaire focuses on the patients’ cardiac health and their experience with a cardiologist. The questions and response choices are as follows:

“Have you personally ever been diagnosed with any of the following cardiac conditions?”Atrial fibrillation, cardiomyopathy, heart stents, congestive heart failure, heart attack, coronary artery disease, hypertension, stroke, and pacemaker or defibrillator“Are you currently being seen by a cardiologist?”Yes: When is your next scheduled appointment? (eg, 03/2030)No: When is your next scheduled appointment with a primary care physician?

### Statistical Analysis

The information collected from the study is categorical data: accurate versus inaccurate. We will be performing an interrater reliability test using Cohen κ coefficient for each of the individuals making a preliminary diagnosis. This will give us a level of agreement. All tests will be 2-sided, and *P* values <.001 will be considered statistically significant.

The number of participants required to achieve statistical significance for this study was calculated to be 655 after completing a power analysis for a 2×2 contingency table design. The probability of a positive diagnosis was .84 and .82 for KardiaMobile and standard ECG, respectively, after applying published literature findings on the efficacy of both methods. Applying Cohen κ statistic, we are looking at the agreement between the 2 metrics to see if KardiaMobile is an effective prescreen. Additional statistical methods include direct comparison, noninferiority, superiority, qualitative comparison, sensitivity, and specificity.

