The number of patients who were screened as having AFib and had an abnormal ECG reading will be compared by using the participant’s medical record on Epic Systems. The number of positive screens versus negative screens will also be compared to assess the sensitivity and specificity of testing in the given population.

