#### Primary Measures

##### Detection Accuracy

The researchers will measure the accuracy of the KardiaMobile ECG device by comparing the resulting ECG phenotype (normal, possible AF, unreadable, unclassified, tachycardia, or bradycardia) to the patients’ actual heart health as determined by the standard 12-lead ECG.

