## Results

As of March 1, 2024, a total of 2339 participants have been enrolled. Of the 6 UF Health specialty clinics, 335 were from the UF Health Nephrology Clinic, 466 from the UF Health Sleep Clinic, 597 from the UF Health Ophthalmology Clinic, 526 from the UF Health Urology Clinic, 231 from the UF Health Neurology Clinic, and 184 from the UF Health Pre-Surgical Clinic. The participants’ ages ranged from 18 to 99 years, with an average age of 61 (SD 10.25) years. The average weight of all participants is 194 (SD 14.26) lbs. The race distribution was reported to be 266 (11.42%) African American, 51 (2.18%) Asian, 124 (5.30%) Latino, 1818 (77.73%) White, and 80 (2.61%) others.

The KardiaMobile rhythm strip reported 381 abnormal readings, which are pending analysis from a cardiologist. A total of 78 readings were labeled as possible AFib, 159 readings were labeled unclassified, and 49 were unreadable. Additionally, 1573 (67.25%) of participants report not regularly seeing a cardiologist.

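### The primary accuracy measure is stated in three ways that no rule links: the accurate/inaccurate variable cannot yield the planned statistics, and a positive screen could mean 78 or 381 readings

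*Protocol article*

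**What the plan says.** Three sections of the protocol article describe the accuracy data.

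- **Primary Measures, Detection Accuracy.** The device output has six labels: "the resulting ECG phenotype (normal, possible AF, unreadable, unclassified, tachycardia, or bradycardia". It is compared with the patient's heart health as determined by the standard 12-lead ECG.
- **Statistical Analysis.** "The information collected from the study is categorical data: accurate versus inaccurate". The same section plans a 2×2 contingency table, Cohen's kappa between the two methods, sensitivity and specificity.
- **Procedure.** "The number of positive screens versus negative screens will also be compared to assess the sensitivity and specificity of testing in the given population". The sentence before it brings in two further terms: "The number of patients who were screened as having AFib and had an abnormal ECG reading will be compared".

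The interim counts are in Results: "The KardiaMobile rhythm strip reported 381 abnormal readings, which are pending analysis from a cardiologist", and "A total of 78 readings were labeled as possible AFib, 159 readings were labeled unclassified, and 49 were unreadable". The Discussion adds that unclassified and unreadable outputs are included in the abnormal findings. No section maps the six labels to accurate or inaccurate, or to positive or negative.

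**The concern.** Each planned statistic needs two values per participant: what the device said and what the reference said. A variable already scored as accurate or inaccurate has merged the two, and the merge cannot be undone.

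The Procedure section does work with positive and negative screens. It leaves open whether a positive is a possible-AFib label or any abnormal label, because it uses both ideas in one sentence. The abnormal group is nearly five times the possible-AFib group (381/78 = 4.9). The choice therefore moves the primary result more than sampling error would. Two analysts who both followed the article could report materially different specificity and kappa from the same strips.

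**Working it through.** **Inputs (Results and Discussion).** N = 2339 participants; 381 abnormal readings; 78 possible AFib; 159 unclassified; 49 unreadable. I assume one reading per participant; the Discussion says that participants were not asked back for another.

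**1. What an accurate/inaccurate flag loses.** Accurate = TP + TN and inaccurate = FP + FN. Two counts cannot give four cells. Suppose 78 of 2339 have AFib, so 2261 do not.

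- Device A misses all 78 and raises no false alarm: accurate = 2261/2339 = 96.7%, sensitivity 0%, specificity 100%.
- Device B finds all 78 and raises 78 false alarms: accurate = (78 + 2183)/2339 = 96.7%, sensitivity 100%, specificity 2183/2261 = 96.6%.

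The flag has the same distribution for both devices. Sensitivity, specificity and kappa cannot be recovered from it.

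**2. What makes up the abnormal readings.**

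- Itemised: 78 + 159 + 49 = 286.
- Remainder: 381 − 286 = 95, which is 24.9% of 381 and 4.1% of 2339. The article states neither this number nor a label for it. By elimination from the six labels, these are presumably tachycardia or bradycardia.
- Unclassified plus unreadable: 159 + 49 = 208, or 8.9% of 2339.
- Normal: 2339 − 381 = 1958.

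**3. Two codings of a positive screen that the text allows.**

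| Coding | Positives | Share of 2339 |
|---|---|---|
| Possible AFib only | 78 | 3.3% |
| Any abnormal reading | 381 | 16.3% |

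**4. Effect on specificity and kappa (illustration).** Assume that all 78 possible-AFib readings are true AFib, that there is no other AFib, and that reference status is known for all. Non-AFib participants number 2339 − 78 = 2261.

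- Possible AFib only: no false positives, so specificity is 2261/2261 = 100% and kappa is 1.00.
- Any abnormal reading: false positives are 381 − 78 = 303 (that is, 159 + 49 + 95). Specificity = 1 − 303/2261 = 86.6%.
- Kappa under the second coding: observed agreement = (78 + 1958)/2339 = 0.870. Chance agreement = (381 × 78 + 1958 × 2261)/2339² = 4,456,756/5,470,921 = 0.815. Kappa = (0.8705 − 0.8146)/(1 − 0.8146) = 0.30.

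**5. Weight of the inconclusive strips.** Keep the 95 as negatives and vary only the 208. If they are excluded, specificity is 2053/2053 = 100%, where 2053 = 1958 + 95. If they are counted as positive, it is 2053/2261 = 90.8%. Any definition that leaves these 208 unassigned is still incomplete.

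**The case against.** **The six-label comparison and the accurate/inaccurate outcome may be one thing.** The first can be read as the comparison and the second as its result. No label-for-label matching rule is stated either. This stands: the two descriptions are not strictly contradictory, and a reader who infers three mutually exclusive endpoints goes too far. It does not rescue the flag as the analysis variable, because the statistics planned in the same section cannot be built from it.

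**The target is plainly AFib.** Specific Aims, the study title under Recruitment, the heading of the flow diagram and the Discussion all say so. This also stands, and it makes the repair straightforward. It still does not say which device labels count as a positive screen, and the Procedure section keeps the abnormal-reading wording in play.

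**A full protocol or analysis plan may hold the mapping.** It may, and a missing mapping alone would be no finding in a condensed article. The point rests on what the article does state: a data form that does not fit its own planned analyses, and two competing terms for the event.

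**Two stronger readings are tempting and unsupported.**

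- One counts the residual 95 with the 78 to get 173 positives (7.4%), and concludes that specificity could not exceed about 95.7–95.9%, below the 97% given in the Discussion. No section defines a positive that way. If abnormal means positive, the 208 unclassified and unreadable strips come in as well. The denominator behind the 97% is not given, and the Procedure section describes a 12-lead ECG only after an irregular finding and at the physician's decision. No comparison with 97% can be drawn.
- The other says that a device always reporting normal would pass as highly accurate. The article does not plan a single percent-accurate result. The sensitivity and kappa that it does plan would both be zero for such a device.

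**Conclusion.** The concern holds as an inconsistently stated primary measure. Two parts are firm from the text: an accurate/inaccurate variable cannot yield the planned 2×2 table, kappa, sensitivity or specificity; and a positive screen is undefined between 78 readings (3.3%) and 381 readings (16.3%).

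The size is illustrative. Specificity of 100% versus 86.6%, and kappa of 1.00 versus 0.30, rest on three assumptions: every possible-AFib reading is true AFib, there is no other AFib, and reference status is known for all 2339. The article does not give the 12-lead results, so the real values will differ. The figure of 95 is a subtraction and its rate-only label an inference; the conclusion depends on neither. Nothing here shows that the sensitivity and specificity reported in the Discussion are wrong. The inconsistency should be settled before the accuracy analysis is finalised, because it decides what the primary result means.

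**What to change.** Use one AFib endpoint in Procedure, Detection Accuracy and Statistical Analysis:

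- **Index positive:** possible AFib. **Index negative:** normal, tachycardia or bradycardia.
- **Reference:** AFib, yes or no.
- **Data:** replace the accurate/inaccurate statement with the paired index and reference values for each participant.
- **Inconclusive:** keep unclassified and unreadable as a separate category and report its rate. Give sensitivity and specificity twice, once excluding these readings and once counting them as positive.
- **Rate labels:** report tachycardia and bradycardia agreement in a descriptive table, not as AFib accuracy.
- **Wording:** remove or define the abnormal-reading term where screening results are compared.

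The cost is rewording and recoding of readings already collected. The downside is that any AFib that the device labels only as a rate abnormality counts as a miss, so sensitivity may be slightly lower.

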## Introduction

### Addressing the Use of Sinus Rhythm Screening

Cardiovascular disease is the leading cause of death in the United States [1]. It is estimated that by 2030, 43.9% of US adults will have at least 1 type of cardiovascular disease [2]. Atrial fibrillation (AFib) is the most common sustained arrhythmia diagnosed in clinical practice [3,4]. It reduces a patient’s quality of life and increases morbidity and mortality rates, which may lead to an increased risk of heart failure [5].

The prevalence of AFib is 2.3% in people older than 40 years and 5.9% in those older than 65 years, and about 70% of individuals with AFib are between 65 and 85 years of age [6]. The prevalence of AFib increases with age, and considering the present aging population, an epidemic is expected to occur within the next 10-20 years [4]. Patients with chronic kidney disease show a higher prevalence of AFib, with ranges estimating from 16% to 21% for patients not on dialysis and 15%-40% for patients on dialysis [4,7]. Currently, about 2.7-6.2 million people in the United States have AFib, but as the population continues to age, an estimated 6-12 million people in the United States will be affected [4,7]. However, since AFib can be asymptomatic, it may remain undiagnosed until or after complications occur. Waiting for these complications to arise may be detrimental, as AFib has a 5-fold increased risk of stroke [8,9]. Developing a low-cost and efficient screening protocol for primary care and outpatient clinics may help to improve the detection of AFib and may help prevent the risk of stroke. In fact, implementing proper treatment, such as the use of oral anticoagulants after a diagnosis of AFib, can decrease the risk of stroke by 60% [5].

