## Methods

### Participants

For this study, we will recruit approximately 655 participants from each of the selected University of Florida (UF) outpatient specialty clinics. This sample size was specifically chosen as a result of statistical analysis that suggests this study population would indicate a powered study. There is no control group, as this was an observational study. Due to the nature of our enrollment process, which does not require a follow-up visit, we expect a <1% attrition rate, reaching a desired ~655 samples per site based on our power analysis. Study participants will be between the ages of 18 and 99 years.

Eligible participants are any patient visiting the UF Nephrology Clinic, UF Sleep Clinic, UF Neurology Clinic, UF Ophthalmology Clinic, UF Urology Clinic, and UF Pre-Surgical Center. Patients with a history of AFib will not be excluded from the study, as they provide valuable data on potential risk factors and may be prone to AFib recurrence. Participants were only excluded if they were younger than 18 years of age, a leg or hand amputee, a paralyzed person, unable to consent, or unable to read and comprehend English.

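### The sample size of 655 and the claim of a powered study are not supported by the stated inputs: .84/.82 cannot be AFib positivity in this sample, and 655 does not follow from them at the stated significance level

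*Protocol article*

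**What the plan says.** All references are to the protocol article.

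- **Statistical Analysis.** The required number "was calculated to be 655 after completing a power analysis" for a 2×2 table. The inputs are: "The probability of a positive diagnosis was .84 and .82 for KardiaMobile and standard ECG, respectively", obtained "after applying published literature findings on the efficacy of both methods". The target is agreement between the two methods, measured by Cohen kappa. Tests are two-sided, and P "values <.001 will be considered statistically significant". No power level, null or alternative kappa, discordance or margin is given.
- **Participants.** The size is attributed to "statistical analysis that suggests this study population would indicate a powered study". Here the number applies per site: "we will recruit approximately 655 participants from each of the selected University of Florida (UF) outpatient specialty clinics". Six sites give 6 × 655 = 3,930. Any patient of the six clinics is eligible, and known AFib is not an exclusion.
- **Introduction.** "The prevalence of AFib is 2.3% in people older than 40 years and 5.9% in those older than 65 years". For chronic kidney disease it gives 16% to 21% off dialysis and 15% to 40% on dialysis.
- **Results.** Among 2,339 enrolled, 381 readings were abnormal. "A total of 78 readings were labeled as possible AFib", 159 were unclassified and 49 unreadable. Nephrology supplied 335 participants.

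**The concern.** In a 2×2 agreement calculation, the probability of a positive diagnosis is a marginal: the share of all participants that a method calls positive. Rates of .84 and .82 would mean about 550 and 537 positives in every 655 people. That cannot describe AFib in patients who merely attend a urology, eye or sleep clinic.

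The values are said to come from literature on efficacy, and the same section describes the data as correct versus incorrect. They may therefore be accuracy or sensitivity figures used in the wrong place.

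The number 655 is the article's only justification of size and sets the per-site target. Detection accuracy is a primary measure, and the precision of kappa and sensitivity depends heavily on how many participants have AFib. If the inputs do not fit the study, readers cannot rely on the statement that it is powered.

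**Working it through.** **1. Can .84/.82 be AFib positivity here?** The article's own rates are:
- 2.3% (over 40) and 5.9% (over 65);
- 16% to 21% and 15% to 40% in kidney disease;
- 78/2,339 = 3.3% possible AFib;
- 381/2,339 = 16.3% any abnormal reading.

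The highest, 40%, is under half of .82. Giving all 335 nephrology participants 40% and the other 2,004 a rate of 5.9% yields (134 + 118)/2,339 = 10.8%. So the values are not AFib positivity.

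**2. If they are sensitivities.** The denominator is then AFib cases, so 655 would have to count cases. Among 655 participants the expected cases are 655 × .023 = 15 to 655 × .059 = 39 at the age-based rates, and 105 to 262 at 16% to 40%.

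**3. Does 655 follow from a difference test?** Assume 80% power (z = 0.8416). The two-sided critical values are z = 3.2905 at .001 and 1.9600 at .05.

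*Independent groups:* n = {[z_α √(2p̄q̄) + z_β √(p₁q₁ + p₂q₂)] / (p₁ − p₂)}², with p̄ = .83.
- At .001: [(3.2905 × .5312 + 0.8416 × .5310)/.02]² = 12,045 per group.
- At .05: 5,537 per group.
- Power with 655 per group: 1.0% at .001 and 15.9% at .05.

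*Paired (McNemar):* n = {[z_α √ψ + z_β √(ψ − d²)] / d}², with d = .02. The discordant share ψ cannot be below .02.
- At .001 and ψ = .02: [(3.2905 × .1414 + 0.8416 × .1400)/.02]² = 851. Any larger ψ needs more.
- At .05, ψ = .0335 gives about 655. That needs an unstated discordance and an alpha other than the one printed.

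So no difference test on these rates at .001 gives 655 with 80% power.

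**4. Does 655 follow from a kappa test?** The contrast is not stated. As an illustration only, take κ₀ = .70 and κ₁ = .80, with the large-sample (Fleiss-Cohen-Everitt) variance V(κ) for fixed marginals:

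n = {[z_α √V(κ₀) + z_β √V(κ₁)] / (κ₁ − κ₀)}²

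Power at n = Φ{[(κ₁ − κ₀)√n − z_α √V(κ₀)] / √V(κ₁)}

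At .84/.82, V(.70) = .928 and V(.80) = .654:
- alpha .05: [(1.9600 × .9634 + 0.8416 × .8088)/.10]² = 660, within 1% of the plan's figure;
- alpha .001: [(3.2905 × .9634 + 0.8416 × .8088)/.10]² = 1,483.

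| Positivity | n at .05 | n at .001 | Power of 655 at .05 | Power of 655 at .001 |
|---|---|---|---|---|
| .84/.82 | 660 | 1,483 | 80% | 22% |
| 2.3% | 4,292 | 9,645 | 14% | 0.4% |
| 3.33% | 2,989 | 6,716 | 20% | 0.7% |
| 5.9% | 1,722 | 3,870 | 35% | 2.5% |
| 16.3% (any abnormal) | 686 | 1,542 | 78% | 21% |

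**5. Sensitivity to the assumed contrast.** With .60 versus .80, power at 655 is above 99% (.05) and 97% (.001) at .84/.82. It is 65% and 8% at 3.33%, and 91% and 33% at 5.9%.

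**6. Pooled sample.** For .70 versus .80 at 3.33%, V(.70) = 4.204 and V(.80) = 2.958. With n = 3,930:
- alpha .05: Φ[(6.269 − 1.9600 × 2.050)/1.720] = 90%;
- alpha .001: Φ[(6.269 − 3.2905 × 2.050)/1.720] = 39%.

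**The case against.** The case for the plan has real content.

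- **Kappa is symmetric in its labels.** Marginals of .84/.82 and .16/.18 give the same 660. The observed abnormal rate is 16.3%, and the accuracy measure scores every device output, not only possible AFib. For an abnormal-versus-normal table, 655 would be about right at .05 under the illustrative contrast. This stands as arithmetic. It does not rescue the text, because the screening target is AFib, 159 + 49 = 208 of the 381 abnormal readings are unclassified or unreadable, and power at .001 is still 21%.
- **Prevalence is not uniformly 2% to 6%.** Those are general-population figures by age. Kidney-disease rates are higher, nephrology is a site, and known AFib is allowed. This stands, and the range must cover it. Even the extreme mix of 10.8% gives only 60% power at .05 and 9% at .001 for .70 versus .80.
- **The planned total is about 3,930.** At 3.3% positivity that is adequate for the illustrative contrast at .05. It is not adequate at .001.
- **The hypotheses and power may sit in a document not shown.** That is fair, and their absence is not the point. The rates, alpha, 655 and the powered claim are all printed, and the printed items do not fit together.

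Three stronger readings are tempting:
- *The powered claim is false.* The test, contrast and power are unstated, a wider kappa contrast changes the answer, and for a fixed 2-point difference low prevalence reduces the number needed. The article does not allow that proof.
- *The inputs overstate cases 14- to 36-fold (.84/.059 to .84/.023), so the shortfall is of that size.* Because of the symmetry, the illustrative kappa sample size rises about 4.5-fold at 3.33% (2,989/660).
- *Every site will hold only 15 to 39 AFib cases, too few for its own sensitivity estimate.* This need not hold for nephrology, and no site-level sensitivity analysis is specified.

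**Conclusion.** The concern holds in this form: 655 and the powered statement are unsupported by the inputs given for them.

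Two parts need no assumed kappa contrast. First, .84/.82 cannot be AFib positivity in an unselected clinic sample. Read as accuracy or sensitivity, they are the wrong quantity for kappa, and as sensitivities they would require 655 AFib cases. Second, at two-sided .001 with 80% power (the power level is my assumption), a difference test on these rates needs 12,045 per group or at least 851 pairs.

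The kappa figures are illustrative. They rest on .70 versus .80, equal marginals away from .84/.82, and the chosen definition of positive. Under them, 655 has about 20% power at .05 and under 1% at .001 when positivity is 3.3%, against 78% and 21% if positive means any abnormal reading.

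The article also gives 655 as the number for the study in one section and for each site in another, so it is unclear what the calculation was meant to size.

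**What to change.** - Withdraw .84/.82 as positivity rates, and withdraw the powered statement. If the values are accuracy or sensitivity figures, label them so.
- Define what counts as positive, including how unclassified and unreadable outputs are handled.
- Restate either the kappa power or the precision of kappa, sensitivity and specificity at realistic AFib positivity: about 3%, with a range that covers nephrology. Give the hypotheses and the alpha actually used.
- Do this for the pooled sample (2,339 enrolled, about 3,930 planned), and say whether 655 is a study total or a site target.
- If precision for positive predictive value on the 78 possible-AFib readings is added, the worst-case half-width is 1.96 × √(.25/78) = ±11 points. Label it a best case on numbers. It assumes all 78 have a reference reading, whereas the Procedure section leaves the 12-lead ECG to the physician in participants without prior arrhythmia.

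The cost is a recalculation, some rewording and a less favourable stated figure. No extra patients are needed.

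### The judgement that KardiaMobile works as a prescreen is tied to Cohen kappa rather than to the planned sensitivity and specificity, and superiority is listed against a comparator that is itself the reference

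*Protocol article*

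**What the plan says.** All references are to the protocol article.

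- **Role of kappa (Statistical Analysis).** Kappa between the device and the standard ECG is the statistic linked to the screening judgement: "Applying Cohen κ statistic, we are looking at the agreement between the 2 metrics to see if KardiaMobile is an effective prescreen". Kappa has a second role, agreement between readers: "We will be performing an interrater reliability test using Cohen κ coefficient for each of the individuals making a preliminary diagnosis".
- **Decision rule (same section).** One rule covers everything: "All tests will be 2-sided", and P "values <.001 will be considered statistically significant". No null or minimum kappa is given.
- **Other methods (same section).** "Additional statistical methods include direct comparison, noninferiority, superiority, qualitative comparison, sensitivity, and specificity". No endpoint or margin is attached to noninferiority or superiority. The Procedure section also plans sensitivity and specificity, without a criterion.
- **Reference standard (Primary Measures, Detection Accuracy).** The device result is compared with the patients' "actual heart health as determined by the standard 12-lead ECG".
- **Sample size inputs (Statistical Analysis).** The number was "calculated to be 655 after completing a power analysis for a 2×2 contingency table design", with these rates: "The probability of a positive diagnosis was .84 and .82 for KardiaMobile and standard ECG, respectively".
- **Who gets a 12-lead (Procedure and its flow diagram).** A 12-lead follows an irregular device reading or is ordered if indicated.

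**The concern.** A prescreen is judged mainly by how many cases it misses, and then by how many false alarms it raises. Kappa merges both errors into one number and scales it by chance agreement, which depends on how common AFib is. The same device can therefore score low in one clinic and high in another, and a device that misses many cases can outscore one that misses few.

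A small P value for kappa does not repair this. Under the usual null of zero it shows only agreement beyond chance. Superiority has a different problem: a comparator that defines the truth makes no errors, so nothing can be more accurate than it.

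What is at stake is the conclusion. The Discussion calls the device an accurate and effective AFib screen, and a kappa result could neither support nor refute that.

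**Working it through.** **Inputs**

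- Prevalence (Introduction): 2.3% over age 40, 5.9% over age 65, and 16%, the lower end of the range given for chronic kidney disease without dialysis.
- Device A, as cited in the Introduction: sensitivity (Se) 98.5%, specificity (Sp) 91.4%.
- Device B, assumed for contrast: Se 50%, Sp 99%.
- Sample size 655 and positive rates .84 and .82 (Statistical Analysis).

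**The plan's own figure.** The 655 does not follow from the stated rates under a paired comparison at the stated threshold. A McNemar test of .84 against .82 at two-sided .001 with 80% power needs at least 851, even at the smallest possible discordance of 2%: (3.29×√.02 + 0.84×√(.02 − .02²))² / .02² ≈ 851. A kappa test can come close to it, but only with null and target values the article does not give. That is a separate matter, and 655 is taken as given below.

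**Step 1. Kappa as a function of prevalence.** With prevalence p:

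- device positive rate q = p·Se + (1−p)(1−Sp)
- observed agreement po = p·Se + (1−p)·Sp
- chance agreement pe = p·q + (1−p)(1−q)
- kappa = (po − pe)/(1 − pe)

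Worked case, p = .023:

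- Device A: q = .1067, po = .9156, pe = .8752, kappa = .0404/.1248 = 0.32.
- Device B: q = .0213, po = .9787, pe = .9567, kappa = .0220/.0433 = 0.51.

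| Prevalence | Kappa, A (98.5%/91.4%) | Kappa, B (50%/99%) |
|---|---|---|
| 2.3% | 0.32 | 0.51 |
| 5.9% | 0.55 | 0.58 |
| 16% | 0.76 | 0.60 |

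Device A's accuracy is the same in every row, yet its kappa more than doubles. At 2.3% and 5.9% kappa ranks B above A, although B misses 50% of AFib and A misses 1.5%. At 16% the order reverses.

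**Step 2. What P<.001 would establish, if the null is kappa = 0.** The large-sample null standard error is √(pe + pe² − S) / [(1 − pe)√n], where S sums, over the positive and negative categories, the product of the two marginal rates times their sum.

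- pe = .82×.84 + .18×.16 = .7176
- S = .82×.84×1.66 + .18×.16×.34 = 1.1532
- standard error = √(.7176 + .5149 − 1.1532) / (.2824×√655) = 0.039
- two-sided .001 critical value 3.29, so the threshold is 3.29 × 0.039 ≈ 0.13

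Any kappa above about 0.13 would be significant. As an illustration at a low prevalence, an assumed device with Se 30% and Sp 91.4% at 5.9% prevalence has expected kappa 0.16, null standard error 0.0376, z = 4.33 and P = 1.5×10⁻⁵. It misses 70% of AFib and passes.

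**Step 3. Superiority.** If the 12-lead is the truth, its sensitivity and specificity are 100% by definition, and KardiaMobile can at best tie. A device positive rate of .84 against a true rate of .82 then means at least 2 points of false positives, about .02 × 655 = 13 participants.

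**Step 4. Precision of sensitivity.** Assume true sensitivity 95% and a reference tracing for all 655. The half-width is 1.96√(.95×.05/cases).

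- 2.3%: 655 × .023 ≈ 15 cases, ±11.0 points
- 5.9%: 655 × .059 ≈ 39 cases, ±6.9 points

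**The case against.** The strongest reply is that the right measures are already in the plan. Sensitivity and specificity appear in both Procedure and Statistical Analysis, and the Discussion reports accuracy in those terms (95% and 97%), not as a kappa. This stands, and it limits the point: the plan's data can address screening accuracy, but the stated judgement is attached to the wrong statistic.

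Several stronger readings are tempting, and the article does not support them.

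- **That kappa is the primary statistic.** It is never called that. The primary measure is detection accuracy against the 12-lead. The link is only the sentence tying kappa to prescreen effectiveness, with sensitivity and specificity listed as additional.
- **That significance against kappa = 0 is the success rule.** No null is named, and the P<.001 rule is a blanket one. Step 2 is conditional on the default null. A null value, threshold or margin may sit in a fuller plan, and its absence from an article is no fault.
- **That noninferiority is meant for positive rates, or is invalid.** The .84 and .82 are given only as power inputs. With a margin on sensitivity or specificity, noninferiority is a legitimate performance goal.
- **That near-equal positive rates could hide a device missing half of AFib at the planned rates.** At .84 and .82 only 16% are device-negative, so at most .16/.82 = 19.5% of reference positives can be missed. The reversal in Step 1 needs low prevalence.

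It would also be wrong to put positive predictive value (PPV) in kappa's place. PPV depends on prevalence and does not count misses. At an illustrative 3.3% prevalence it is 52% for a 95%/97% device and 63% for a 50%/99% device.

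**Conclusion.** The point holds in a limited form. The article ties its prescreen judgement to a statistic that can rank devices the wrong way round: at 2.3% prevalence, 0.32 for the cited device against 0.51 for one that misses half of AFib. It also lists superiority, which in terms of accuracy is impossible against a comparator defined as the truth.

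The kappa comparison rests on the prevalences and device performance cited in the Introduction and on one assumed contrast device. The 0.13 threshold rests on a null of zero. The objection to superiority needs no figures beyond the definition of the reference. The plan should be changed, but it is not devoid of suitable accuracy measures.

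**What to change.** Revise the Statistical Analysis section as follows.

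1. Base the prescreen conclusion on the already planned sensitivity and specificity for AFib against the 12-lead. Report each with a 95% confidence interval, and judge the lower bound against a minimum fixed in advance.
2. Because 12-leads follow irregular readings, limit those claims to participants whose 12-lead did not depend on the Kardia result, for example where such a tracing is already in the medical record. Elsewhere report PPV only as a supplementary estimate, not as the success criterion.
3. Keep kappa as a descriptive estimate with a confidence interval, chiefly for agreement between readers.
4. Delete superiority. Keep noninferiority only as a performance goal with a stated margin on sensitivity or specificity.

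**Cost.** Items 1, 3 and 4 are changes of wording. Item 2 means identifying the eligible tracings in the record. The article does not say how many exist, and if there are too few, obtaining more would need an added procedure. A significant kappa could no longer be claimed as success. The sensitivity interval will be wide: about 15 to 39 AFib cases per 655 at 2.3% to 5.9% prevalence if everyone were verified, and fewer in a subset.
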